We hypothesise that the behavioural intention related to the implementation of appropriate asthma self-management will improve at the end of the rehabilitation program (T2). As mentioned above, the behavioural intention is considered a key determinant of successful asthma self-management at work [15, 20]. Then, after 3 months and the possible return to work (T3), actual asthma self-management at work should have improved due to prior proactive initiation of changes of relevant individual working conditions. Thus, behavioural intention will be used as primary outcome at T2 while asthma self-management will serve as primary outcome at T3. Self-management-related knowledge and self-efficacy along with other factors (see below) will represent the secondary outcomes. The potential improvement in asthma self-management at work and related improvement in asthma control, asthma-related quality of life, and the subjective employment prognosis (see above) [6, 7] could then reduce the number of exacerbations and sick days (and also related costs). Therefore, we will also examine asthma control, asthma-related quality of life, the subjective employment prognosis, and the number of exacerbations and sick days as secondary outcomes.

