### Sample size

We assume that over a period of 11 months, we will be able to recruit approximately 300 individuals who meet the inclusion criteria (Bad Ems: *n* ≥ 100, Bad Reichenhall: *n* ≥ 200). With a drop-out rate of 40% by T3, we can assume a sample of 180 participants (90 per group) attending at all measurement time points (Bad Ems: *n* ≥ 60, Bad Reichenhall: *n* ≥ 120). With an intermediate effect size of Cohen’s d = 0.5 [24], an alpha level of 0.05, and a statistical power of 0.8, this sample size should be sufficient to detect significant differences and the sample size is comparable to or exceeds that of similar RCTs [25–28].

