### Data analysis plan

The primary statistical analysis will be based on the intention-to-treat (ITT) sample, that is, all participants as randomized. Since the ITT includes all participants for whom treatment was intended, data from individuals who, for example, did not ultimately receive the intervention or did not receive it completely (e.g., due to premature drop-out) are also included in the evaluation. Thus, the evaluation strategy based on the ITT principle is assumed to resemble outcomes that may be achieved in everyday life. Therefore, a secondary analysis based on the per-protocol collective (PP) will be performed. Here, all participants are excluded for whom the study treatment deviated from the study protocol (e.g., no participation in session 1 and/or 2). Since the PP only includes those participants who completed the study in compliance with the study protocol, the results may be biased in favour of the intervention. If the evaluation of the primary outcomes (see above) according to the ITT and PP principles provides similar results, confidence in the reliability of findings increases. If this is not the case, then possible reasons for the discrepancy between the two approaches will be discussed [43, 44].

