The following describes the analyses in detail: Descriptive statistics, including means for continuous variables and proportions for categorical variables, will be used to summarize participant characteristics. We will determine the potential changes in primary and secondary outcomes (T1 to T2, T1 to T3) by pre-post comparisons within groups and test them for statistical significance using paired t-tests. Differences between groups (at T2 and T3) will be evaluated using univariate analyses of covariance (ANCOVAs). That is, membership in the intervention or control group will be used as the independent variable in each case, and the follow-up score of the primary outcome measures (behavioural intention, asthma self-management at work) and secondary outcome measures (self-efficacy, self-management-related knowledge, number of sick days, number of exacerbations, asthma control, asthma-related quality of life, and subjective employment prognosis) will be used as the dependent variable. Initially, only the corresponding baseline value of the primary outcome variable is included as a covariate to remove conditional bias [45, 46]. In a next step, the rehabilitation clinic [47], gender, age [48], and education [48] are additionally included as covariates. If the correlation between baseline and follow-up values is high (> 0.5), change scores are used as independent variables instead of follow-up values, as these then provide a more precise estimate [49]. For all models, the statistical model assumptions (linearity, homoscedasticity, normality of residuals) are tested. If the model assumptions are violated, appropriate analysis methods (e.g., robust regression, log transformation) are applied. In addition, to test whether comorbid COPD or long/post COVID disease affects the outcomes, sensitivity analyses will be performed excluding participants with COPD and/or long/post COVID symptoms. We will also conduct the analyses again without those who participated during the pre-test^2^, as at this point there may not yet be a routine regarding the training procedures and minor adjustments may still be made. Gender-stratified analyses are also conducted. Likewise, those with uncontrolled (ACT < 20 [32]) versus controlled asthma (ACT ≥ 20 [32]) and those with versus without a need for medical-occupational rehabilitation^3^ should additionally be analysed separately. Our primary analysis will be based on complete case analysis. In case the proportion of missing data exceeds 5% on a given variable, we will carry out sensitivity analysis employing multiple imputations.

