## Discussion

Observational data suggested that psychosocial working conditions are associated with asthma self-management at work among employed individuals who are undergoing inpatient rehabilitation for asthma [4, 5]. Key working conditions included social support and job decision latitude, i.e., the extent to which work tasks and times can be determined at one’s own discretion [4, 5]. To our knowledge, experimental data from pulmonary rehabilitation on this issue are lacking. The aim of this study is therefore to develop and implement a novel patient education module that seeks to empower individuals with asthma to modify their working conditions in order to maximize their opportunities for appropriate asthma self-management at work.

Based on the assumption that the expected effects are observed, the patient education module could increase, amongst others, work ability, and social participation, improve return to work or staying at work, and reduce the number of sick days by improving asthma self-management as well as asthma control and asthma-related quality of life. Improving asthma self-management at work, but also asthma control and asthma-related quality of life [6, 7], could reduce costs associated with, e.g., asthma-related disability and early retirement. Ultimately, a patient education module should be available that is not only applicable to rehabilitation patients with asthma, but could also be evaluated in outpatient settings (e.g., disease management programs) or adapted to other chronic conditions.

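### The T3 primary analysis is described as covering everyone randomised but is run on complete cases, with 40% drop-out forecast and imputation kept as a sensitivity analysis

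*Protocol article*

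**What the plan says.** The Data analysis plan in the protocol article defines the primary population: "The primary statistical analysis will be based on the intention-to-treat (ITT) sample, that is, all participants as randomized". It adds that data from people who did not receive the intervention, or "did not receive it completely (e.g., due to premature drop-out) are also included in the evaluation".

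Later in the same section, after the ANCOVA models, comes the missing-data rule: "Our primary analysis will be based on complete case analysis". Imputation follows as a conditional extra: "In case the proportion of missing data exceeds 5% on a given variable, we will carry out sensitivity analysis employing multiple imputations".

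The Sample size section starts from about 300 recruits and gives the expected loss: "With a drop-out rate of 40% by T3, we can assume a sample of 180 participants (90 per group) attending at all measurement time points". Under Randomization, patients are allocated at the start of rehabilitation, so any loss between then and T3 comes after allocation.

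The Data analysis plan also relies on a comparison with the per-protocol set. Similar intention-to-treat and per-protocol results for the primary outcomes are to raise confidence in the findings.

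**The concern.** An ANCOVA on complete cases cannot contain a participant who has no T3 score. If two in five are lost, the T3 primary result (asthma self-management at work) is estimated in the responders, while the plan says that it covers everyone randomised. Randomisation protects the comparison of the full arms. It does not by itself protect a comparison of those who choose to reply three months after discharge.

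Two features of the plan make this more than a matter of labelling. First, the method that would use the non-responders' T1 and T2 data is ranked below the one that ignores them, although the forecast loss already exceeds the trigger. Second, the per-protocol comparison offers no protection here. Under complete-case analysis both sets omit T3 non-responders, so their agreement says nothing about attrition.

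**Working it through.** **1. The plan's own figure.** Inputs from Sample size: about 300 recruited, 40% drop-out by T3.
- 300 × (1 − 0.40) = 180, or 90 per arm. By clinic, 100 × 0.60 = 60 and 200 × 0.60 = 120. All match the plan.
- Left out of the T3 primary ANCOVA: 300 − 180 = 120, if all losses follow randomisation.
- The Abstract instead gives n ≥ 180 as the number recruited and randomised. Read literally, 180 × 0.60 = 108 would remain. The fraction left out is 40% either way.

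**2. Power is not the issue.** For d = 0.5 and two-sided alpha 0.05 (sidedness is not stated), 80% power needs 63 per arm by the normal approximation. With 90 per arm, power is about 0.92. The question is bias and population.

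**3. The imputation trigger.** Forecast 40% ÷ threshold 5% = 8. On the plan's own expectation, imputation will be run for the T3 outcome, but only as a sensitivity analysis.

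**4. When complete cases are enough.** If only the T3 outcome is missing, and missingness depends only on arm and the covariates in the model, the complete-case ANCOVA is unbiased for all randomised participants. The first model has the baseline score only; the second adds clinic, gender, age and education. Missingness that also depends on T2 responses, or on the unseen T3 value, breaks the condition.

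**5. Illustrations of size.** The inputs below are assumptions, not figures from the protocol.
- *Unequal drop-out, same gap in both arms.* If non-responders score g worse than responders, and a fraction p drops out, the responder mean exceeds the arm mean by p × g. The shift in the between-arm difference is g × (p_I − p_C), where I is the intervention arm and C the control arm. With g = 0.5 SD and 35% against 45%, the size is 0.5 × 0.10 = 0.05 SD. It runs against the module if the intervention arm loses 35%, and in its favour if that arm loses 45%.
- *Equal drop-out, gap in one arm only, no true effect.* The shift is 0.40 × g. For g = 0.25 it is 0.10 SD; for g = 0.5 it is 0.20 SD. With 90 per arm the standard error is √(2/90) = 0.149 SD, and the two-sided 5% error becomes about 10% or 27%.
- *Effect differs between responders and non-responders.* The all-randomised effect is 0.6 × d_resp + 0.4 × d_non. With d_resp = 0.5 and d_non = 0.25, 0 or −0.25, it is 0.40, 0.30 or 0.20. Complete cases report 0.50 throughout.

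The three cases differ in size and the first can take either sign, so they show a range and not an expected bias.

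**The case against.** The strongest defence is that the two statements concern different things. The intention-to-treat passage deals with incomplete treatment, in contrast to a per-protocol set that excludes people who missed a session. The complete-case sentence deals with missing data. This stands in part: someone who skipped sessions but returned the T3 questionnaire is analysed in the allocated arm. It does not rescue the claim to cover everyone randomised, which fails for anyone without a T3 score.

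A second defence is that imputation is in effect already planned, and that study assistants will telephone T3 reminders. Both are true. What remains is which analysis yields the primary result, and under what assumption.

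Several stronger readings are tempting but are not supported:
- *That exactly 120 randomised people are lost.* Recruitment begins with screening about four weeks before rehabilitation, and the article does not say that all the drop-out comes after allocation.
- *That T2 data on later drop-outs are discarded.* Behavioural intention at T2 is a primary outcome with its own between-group ANCOVA. The T2 data are only unused in the T3 model.
- *That the T3 effect is overstated by 67% (0.50 against 0.30).* This rests on an invented zero effect in non-responders. A missing-at-random analysis would not reliably recover 0.30 either.
- *That missingness is tied to treatment through return to work.* The Discussion hopes that the module could "improve return to work or staying at work", but nothing says that people not back at work will fail to reply. Table 2 schedules the T3 questionnaire without a work-status condition.
- *That the planned imputation would merely repeat the complete-case answer.* The article does not specify the imputation model, and that detail may properly sit in a statistical analysis plan.

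**Conclusion.** The point holds as a conflict between the stated population and the stated missing-data rule for T3. On the plan's forecast, 40% of participants are absent from the T3 primary ANCOVA (about 120 of 300 if losses follow randomisation). The estimate applies to all randomised participants only under an assumption that the article neither states nor defends. No separate drop-out rate is given for T2, where the loss may be smaller.

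It does not follow that the T3 estimate will be biased, or in which direction. Complete-case ANCOVA is valid if missingness depends only on arm and covariates, and the documents do not show whether it does. The matter should be settled before analysis because it decides which number is the T3 primary result.

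**What to change.** Make the T3 primary analysis include all randomised participants under a stated missing-at-random assumption, in one of two ways:
- a likelihood-based repeated-measures model of the outcome, set up so that people with T1 data only are retained; or
- multiple imputation by arm, using T1 and T2 data: the outcome itself, behavioural intention, self-efficacy, knowledge and ACT, with clinic, age, gender and education.

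T3 work status should not be relied on as a predictor, because it will be missing for the same people.

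Make complete-case analysis a sensitivity analysis, and drop the 5% trigger for the primary outcomes. Add a delta-adjusted sensitivity analysis at T3, because a missing-at-random model does not cover missingness that depends on the unseen T3 outcome. Report missingness by arm. State how many of the roughly 300 are expected to be randomised, and reconcile this with the Abstract.

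The cost is analysis-plan wording and some programming. No new data are needed, since Table 2 already schedules these questionnaire measures at T1 and T2. The small downside is that the primary result then depends on a stated model for the missing values.

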## Discussion

Observational data suggested that psychosocial working conditions are associated with asthma self-management at work among employed individuals who are undergoing inpatient rehabilitation for asthma [4, 5]. Key working conditions included social support and job decision latitude, i.e., the extent to which work tasks and times can be determined at one’s own discretion [4, 5]. To our knowledge, experimental data from pulmonary rehabilitation on this issue are lacking. The aim of this study is therefore to develop and implement a novel patient education module that seeks to empower individuals with asthma to modify their working conditions in order to maximize their opportunities for appropriate asthma self-management at work.

Based on the assumption that the expected effects are observed, the patient education module could increase, amongst others, work ability, and social participation, improve return to work or staying at work, and reduce the number of sick days by improving asthma self-management as well as asthma control and asthma-related quality of life. Improving asthma self-management at work, but also asthma control and asthma-related quality of life [6, 7], could reduce costs associated with, e.g., asthma-related disability and early retirement. Ultimately, a patient education module should be available that is not only applicable to rehabilitation patients with asthma, but could also be evaluated in outpatient settings (e.g., disease management programs) or adapted to other chronic conditions.

## Data Availability

No datasets were generated or analysed during the current study.

## Abbreviations

ACT: Asthma Control Test
ANCOVA: Analyses of covariance
AQLQ–M: Marks Asthma Quality of Life Questionnaire
COPD: Chronic Obstructive Pulmonary Disease
FEV1: Forced expiratory volume in 1 s
FeNO: Fractional exhaled nitric oxide
IASUM: Institute for Occupational, Social and Environmental Medicine
ICD: International Statistical Classification of Diseases and Related Health Problems
ITT: Intention-to-treat
MBOR: Medical-occupational rehabilitation
MCID: Minimal clinically important difference
PP: Per protocol
RCT: Randomized controlled trial
SPE–scale: Brief Scale Measuring the Subjective Prognosis of Gainful Employment
sR_tot_: Total specific airway resistance
Ig E: Total immunoglobulin E
TPB: Theory of Planned Behaviour
VC: Vital capacity
